### Primary outcome

The primary endpoint will be motor axon reinnervation in the thenar muscles. This will be done using MUNE, a non-invasive electrophysiological technique. Initially introduced in the 1970s [19, 20], multipoint stimulation, the most commonly used MUNE technique, has been shown to be a reliable test for measuring motor axon reinnervation [5]. Apart from providing an objective assessment of large myelinated nerve fibers, MUNE will also serve as a screening tool for eligibility for the trial. To quantify treatment response, MUNE will be repeated at 3, 6 and 12 months post-operatively.

### Secondary outcomes

Secondary outcomes of the study focus on sensory function restoration and functional outcomes. Measures will include:Two-point discrimination (Aβ fibers) using Dellon-MacKinnon DiskPressure sensitivity (Aβ fibers) using Semmes-Weinstein monofilamentCold threshold (Aδ fibers) and pain threshold (C fibers) using CASE IV quantitative sensory testing (QST) equipmentBoston CTS Questionnaire to monitor symptom severityDisabilities of the Arm, Shoulder and Hand (DASH) questionnaire for functional outcomesMoberg Pick-up Test to measure hand dexterity and functional performance

All outcome measures will be monitored at baseline, 3 months, 6 months and 12 months. Sensory testing of peripheral nerves provides more of a challenge, given the multiple fiber types that provide sensory feedback. The above list of tests is designed to capture the full range of sensory fiber functions. A major advantage of QST is that it provides an objective means of measuring the function of different classes of nerve fibers with good reliability. The DASH and the Boston questionnaires used to evaluate symptom severity are both well validated in CTS [21]. Finally, to objectively measure hand functional performance, the Moberg Pick-up Test is a validated tool for CTS with good reliability [22]. All primary and secondary outcome measures will be performed by the same investigators (MC, KMC). To verify the inter-rater reliability of these tests, a subset of patients will undergo separate assessment by two investigators independently in a blinded manner.

### Interventions

Patients will be assigned to either the placebo or ALCAR arm of the study. Both placebo and ALCAR will be fabricated by the same pharmaceutical company (Sigma-Tau, Rome, Italy). They are identical in appearance and taste. Upon arrival, the tablets will be packaged by the pharmacy into identical boxes labeled with a random sequence code. Both groups will undergo open carpal tunnel release without epineurolysis performed by experienced hand surgeons (JO, MM). Post-operatively, patients will take the medications for 2 months. Patients randomized to the ALCAR arm will take 3,000 mg orally divided in three times per day dosing, while the control group will take a matched placebo. The dosing schedule for the study drug was chosen based on previous work by Bianchi et al. (2005) that showed good tolerability and efficacy [23].

### Sample size

Initially, a pilot study of 20 patients will be carried out. Evaluation of the effect size will be based on the primary outcome MUNE. This will provide the necessary data for the sample size calculation for a fully powered large-scale study.

### Statistical analysis

Demographic data will be compiled and analyzed for differences using a Student’s *t*-test and Fisher’s exact test. The primary and secondary outcome measures will be analyzed using two-way ANOVA with the treatment groups and time points being the independent factors. If significant associations are detected, a post hoc analysis will be done for pairwise comparisons. Due to the exploratory nature of the study, sample size calculations and formal analysis of missing data will not be undertaken.

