**Methods:**

In this pilot study we will utilize a double-blind, randomized, placebo-controlled design. Inclusion criteria will include adult patients with severe CTS. This will be confirmed by nerve conduction studies and motor unit number estimation (MUNE). Only those with severe motor unit loss in the thenar muscles (2 standard deviations [SD] below the mean for the age group) will be included. Eligible patients will be randomized to receive 3,000 mg/day of ALCAR orally or placebo following carpal tunnel release surgery for 2 months. The primary outcome will be MUNE with supplementary secondary outcome measures that include: 1) two-point discrimination; 2) Semmes-Weinstein monofilaments for pressure sensitivity; 3) cold and pain threshold for small fiber function; 4) Boston self-assessment Carpal Tunnel Questionnaire and 5) Disabilities of the Arm, Shoulder and Hand (DASH) questionnaire for symptom severity; and 6) Purdue Pegboard Test for hand functional performance. To follow post treatment recovery and monitor safety, patients will be seen at 3 months, 6 months and 1 year. The outcome measures will be analyzed using two-way ANOVA, with treatment assignment and time points being the independent factors. If significant associations are detected, a post hoc analysis will be completed. We aim to recruit ten patients into each of the two groups. Data from this pilot will provide the basis for power calculation for a full-scale trial.

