### Subjects

All patients referred to either the plastic surgery clinics or the EMG lab will be eligible to be screened. Inclusion into the study will be based upon the criteria listed in Table 1. Patients meeting eligibility criteria will be recruited and informed consent will be obtained. They will then undergo motor unit number estimation (MUNE) to quantify the severity of motor axonal loss. Only those with motor axonal loss of > 2 SD below the mean for the age group will be included in the study.

**Table 1 Tab1:** Inclusion and exclusion criteria for patient selection

Inclusion criteria	Exclusion criteria
1) Age > 18 years	1) Motor unit loss in the median nerve less than 2 standard deviations below the mean for the age group
2) One or more of the following symptoms of CTS	2) Presence of other neurologic conditions
a) Numbness and paresthesias in the median nerve distributions	3) Previous carpal tunnel release
b) Precipitation of those symptoms by repetitive motions that are relieved by rubbing and/or shaking	4) Cognitive impairment that renders the patient incapable of providing consent
c) Nocturnal awakening of the above symptoms	5) History of seizures
d) Weakness of thumb abduction and thenar atrophy	6) Kidney disease/renal impairment
	7) Sensitivity to any of the drug components of the formulation or are
	8) Pregnant/breast feeding
	9) For women of child-bearing potential, those that are not willing to use adequate contraceptive prevention methods for at least 30 days after the last dose of the medication.

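### Baseline significance tests at ten per arm cannot inform interpretation, and the MUNE model leaves out age and baseline MUNE, losing precision in the estimate meant to size the full trial

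*Protocol article*

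**What the plan says.** - **Baseline comparison.** The Statistical analysis section states: "Demographic data will be compiled and analyzed for differences using a" Student's t-test and Fisher's exact test. It gives no significance level, no threshold for a material imbalance, and no consequence of a significant or non-significant result.
- **Outcome model.** The same section fixes the analysis of primary and secondary outcomes as "two-way ANOVA with the treatment groups and time points being the independent factors". The abstract names the same two factors. No covariate is named.
- **Size.** The abstract says "We aim to recruit ten patients into each of the two groups", and the Sample size section says "Initially, a pilot study of 20 patients will be carried out". The MUNE effect from this pilot is to supply the data for sizing a full-scale study.
- **Age and baseline MUNE.** The Subjects section sets eligibility against age norms: "Only those with motor axonal loss of > 2 SD below the mean for the age group will be included in the study". The Secondary outcomes section lists baseline as one of the assessment times for all outcome measures, and the Primary outcome section also uses MUNE for screening. Both age and baseline MUNE will therefore be on file for every patient.
- **Randomization section.** No stratification is described.

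**The concern.** A test for baseline differences asks whether the arms differ by more than chance. Under randomisation that is already known: they do not. The p-value then says nothing about what matters, which is how large the realised imbalance is and how strongly the variable predicts the outcome.

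The protocol accounts for age when it selects patients on MUNE but not when it analyses MUNE as the primary endpoint. Variation explained by age or by baseline MUNE, unless the time factor absorbs it, stays in the error term, and a chance imbalance on either is not corrected in the one trial that will be run. The estimate affected is the one on which the next trial's sample size will rest.

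**Working it through.** The plan states no figure on this point, so there is none to reproduce.

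**Inputs.** n = 10 per arm (abstract; 20 in total in the Sample size section). Significance level: not stated, taken as two-sided 5%, with 10% also shown. Covariate-outcome correlation r: not stated, assumed over a range.

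**1. What the t-test can flag.** The standard error of a difference in means, in SD units, is sqrt(2/10) = 0.447. With 18 degrees of freedom the critical value is 2.101, so the smallest significant observed gap is 2.101 × 0.447 = 0.94 SD. At a two-sided 10% level it is 1.734 × 0.447 = 0.78 SD. An observed gap of 0.5 SD gives t = 0.5/0.447 = 1.12, p = 0.28.

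**2. What Fisher's test can flag.** An observed 3/10 against 7/10 gives p = 0.18. It takes 2/10 against 8/10 to reach p = 0.023.

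**3. How often chance gaps pass.** Assume simple randomisation and a normally distributed covariate. The probability of a gap of at least 0.5 SD is 2 × P(Z > 1.118) = 0.26. In 400,000 simulated 10-against-10 trials, 81% of such gaps were non-significant at 5%. The share of all trials carrying one unflagged is 0.26 × 0.81 = 0.21. The 0.5-SD threshold is an illustration; the plan sets none.

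**4. What adjustment would gain.** Adding k covariates to a two-group comparison with N = 20 multiplies the variance of the treatment difference by about

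(1 − R²) × [1 + k/(N − 2 − k − 1)],

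where R² is the share of within-arm outcome variance explained. The bracket is the average cost of chance imbalance.

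- One covariate: the bracket is 1 + 1/16 = 1.0625.
  - r = 0.3: 0.91 × 1.0625 = 0.97
  - r = 0.5: 0.75 × 1.0625 = 0.80
  - Break-even: r² = 1 − 16/17 = 1/17, so r = 0.24
- Two covariates (age and baseline MUNE): the bracket is 1 + 2/15 = 1.133. Break-even: R² = 1 − 15/17 = 0.12 jointly.

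Age alone therefore gives a small gain or a small loss if it is a weak predictor, and a useful gain if it is a moderate one.

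**The case against.** Several points on the other side stand.

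- **No decision hangs on the tests.** A reader might infer that a non-significant result will be used to certify the arms as alike and to justify leaving age out. That is a natural suspicion, but the article does not say so. The MUNE model is the same whatever the tests show, so removing the p-values alone alters no estimate.
- **Bias.** A reader might infer that the treatment estimate is biased by age, or that the baseline tests are the only safeguard. Neither follows. Randomisation is the safeguard, and across repetitions the unadjusted difference is unbiased. Chance age imbalance is already part of its standard error of about 0.45 SD. A shift computed only in trials picked for a large unflagged gap describes a selected subset and depends on assumed correlations.
- **Baseline MUNE may already help.** If baseline is one level of the time factor, a treatment-by-time contrast removes any constant effect of age on MUNE level, leaving only an effect of age on recovery. The section does not name that contrast as the test of effect, so this is possible but not secured.
- **Age may predict weakly here.** Age-specific norms show that reference values vary with age. They do not show that age predicts recovery among patients all selected to lie far below their age mean. The correlation could fall below 0.24.
- **Pilot status.** The Limitations section says openly that the study is exploratory and likely underpowered. That lowers the stakes, but it does not address baseline testing or adjustment.

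A fuller analysis plan might add covariates. The article, however, states both the baseline tests and the two model factors, so the comment concerns a stated choice and not an omission.

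**Conclusion.** The point holds, with minor severity. The planned baseline tests answer no open question in a randomised trial. At ten per arm they flag only observed gaps above about 0.94 SD (0.78 SD at a 10% level), and about one trial in five would carry a gap of 0.5 SD or more that they do not flag. The stated outcome model does not use age or, as a covariate, baseline MUNE, although both are collected and the eligibility rule itself relates MUNE to age.

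The consequence is lost precision and uncorrected chance imbalance in a single small trial, not systematic bias, and the documents do not show that the tests will be used to declare the arms comparable. The size of the loss depends on a correlation that the documents do not give: about 3% of the variance at r = 0.3, about 20% at r = 0.5, and a net cost below about 0.24. The calculations also assume a two-sided 5% level, simple randomisation and roughly normal covariates.

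**What to change.** In the Statistical analysis section:

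1. Replace the baseline tests with a descriptive table by arm (mean and SD, or counts), without p-values.
2. State that follow-up MUNE will be analysed with age, and preferably baseline MUNE, as pre-specified covariates, whatever balance is observed.

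This takes about two sentences and no new data. Each covariate uses one degree of freedom out of 20 patients. Age alone repays that only if its correlation with the analysed outcome exceeds about 0.24; the pair repays it if together they explain more than about 12% of the within-arm variance. If the sponsor judges age unlikely to reach that level in this selected population, baseline MUNE alone is a defensible choice, provided it is fixed before unblinding.

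### The stated two-way ANOVA names no patient term although the same 20 patients are measured at up to four visits; run as written, its two treatment tests err in opposite directions

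*Protocol article*

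**What the plan says.** Statistical analysis in the Protocol article states: "The primary and secondary outcome measures will be analyzed using two-way ANOVA with the treatment groups and time points being the independent factors". The Abstract (Methods) says the same: "The outcome measures will be analyzed using two-way ANOVA, with treatment assignment and time points being the independent factors". Both name two factors and no others.

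The visits are repeated on the same people. For the primary outcome, "MUNE will be repeated at 3, 6 and 12 months post-operatively", following the MUNE done at screening. Under Secondary outcomes, "All outcome measures will be monitored at baseline, 3 months, 6 months and 12 months". The size is small: "Initially, a pilot study of 20 patients will be carried out", and "We aim to recruit ten patients into each of the two groups".

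The follow-on step depends on the ANOVA: "If significant associations are detected, a post hoc analysis will be done for pairwise comparisons". The article does not mention repeated measures, a patient or random effect, a mixed model or a covariance structure. It also does not say whether the treatment main effect or the treatment-by-time interaction is the efficacy test, or whether baseline is a level of the time factor.

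**The concern.** Treatment varies between patients and time varies within them, so the two need different error terms. An ordinary two-way ANOVA has one residual, which mixes between-patient and within-patient variation. For the treatment main effect that residual is too small a yardstick, because four visits from one patient are counted as four separate pieces of evidence. For treatment-by-time it is too large, because stable differences between patients, which cancel out of that comparison, remain in the error.

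The objective is efficacy, and the pairwise comparisons are opened by significance in this model. A test with the wrong error rate could open them too readily or hardly at all. The Limitations section concedes low power and multiple comparisons but does not mention within-patient correlation.

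**Working it through.** The article gives no power, significance level, standard deviation or correlation, so there is no stated figure to reproduce. The check is of the model's error rates.

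**Inputs from the article:** n = 10 per arm; T = 4 visits (or 3 if only post-operative visits enter); factors treatment and time.

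**Assumptions:** two-sided 5% level; total variance 1 at each visit; the same correlation ρ between any two visits of a patient, with ρ from 0.3 to 0.8; complete data; interaction included in the model.

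**Degrees of freedom.** As written: 2 × 10 × 4 = 80 observations less 8 cell means leaves 72. The between-patient test of treatment has 20 − 2 = 18.

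**Treatment main effect.** The model takes the variance of the difference between arm means as 2/(nT) = 2/40 = 0.050. The true variance is (2/nT) × [1 + (T − 1)ρ]. At ρ = 0.5 that is 0.050 × 2.5 = 0.125, so the standard error is 0.354 and not 0.224. The approximate type I error is 2 × {1 − Φ(1.96/√[1 + (T − 1)ρ])}. At ρ = 0.5 and T = 4, 1.96/√2.5 = 1.24, which gives 21.5%.

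**Treatment-by-time.** Under no effect, the interaction mean square has expectation 1 − ρ, but the residual it is divided by has expectation 1. The F ratio is therefore centred near 1 − ρ and rejects too seldom.

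Simulated type I error under no drug effect, 40,000 trials per setting:

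| ρ | Main effect, 4 visits | Formula, 4 visits | Main effect, 3 visits | Interaction, 4 visits |
|---|---|---|---|---|
| 0.3 | 15.3% | 15.5% | 12.2% | 1.4% |
| 0.5 | 21.6% | 21.5% | 16.6% | 0.3% |
| 0.7 | 26.6% | 26.6% | 20.8% | 0.01% |
| 0.8 | 29.1% | 28.8% | 22.6% | about 0% |

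At ρ = 0 the main-effect test holds its level (5.1%). With a patient term, both tests stay between 4.7% and 5.1% across the table's settings.

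**Interaction power** for an assumed effect of 1 SD at all three follow-up visits and none at baseline. The effects (0, 1, 1, 1) have mean 0.75 and sum of squared deviations 0.75, so with a patient term the noncentrality is (10/2) × 0.75/(1 − ρ) = 3.75/(1 − ρ).

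| ρ | Noncentrality | As written | With patient term |
|---|---|---|---|
| 0.3 | 5.36 | 24% | 44% |
| 0.5 | 7.50 | 18% | 58% |
| 0.7 | 12.50 | 13% | 83% |
| 0.8 | 18.75 | 9% | 95% |

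**What is not badly affected.** Under the same assumptions the residual mean square averages 1.00 at every ρ, so it is unbiased for the single-visit variance. A between-arm contrast at one visit using that residual rejects about 5% to 6% of the time under the null. This depends on equal variances. If the baseline SD were half the follow-up SD, the pooled variance would be (0.25 + 3)/4 = 0.8125, and a follow-up contrast would reject about 2 × {1 − Φ(1.96 × √0.8125)} = 2 × {1 − Φ(1.77)}, or roughly 8%.

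**The case against.** The strongest reply is that two-way ANOVA over treatment and time may be shorthand for its repeated-measures form, and that the error term belongs in the full protocol or an analysis plan not shown here. In this context independent factors most naturally means explanatory variables. A reader might infer that the article declares the observations independent; it does not. This limits the point to what happens if the stated model is followed. It does not remove the point, because the article names the model and its factors twice, and nothing in it supports the repeated-measures reading.

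A reader might also take the main effect to be the efficacy claim and conclude that the trial will produce several-fold false positives. The article does not say so. Its hypothesis, which includes faster symptom resolution, fits the interaction at least as well, and on that test the stated model loses power and does not inflate error.

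A third tempting inference is that a wrong standard error would pass into the full-scale trial. The Sample size section says only that the effect size will be evaluated on MUNE. As shown above, the residual SD is usable for planning a single-visit comparison under equal variances.

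Finally, four visits with equal variance and correlation is one setting. Entry is restricted to patients with severe motor unit loss, so baseline MUNE may vary less than later values. The three-visit figures are lower but still well above 5%.

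The pilot's exploratory status, with "Due to the exploratory nature of the study, sample size calculations and formal analysis of missing data will not be undertaken", lowers the stakes. It excuses low power, but not a test whose error rate is not what it claims.

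**Conclusion.** The point holds as a fault in the stated model. Followed literally, the two-way ANOVA uses the wrong error term for both treatment tests. The direction is certain for any positive within-patient correlation. The size is not, since the correlation is assumed.

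Over ρ from 0.3 to 0.8, the main effect's error rate is about three to six times nominal with four visits and somewhat less with three. The four-visit interaction test almost never rejects under the null and gives up between about 20 and 86 percentage points of power (44% − 24%; 95% − 9%) in the 1-SD example. Which harm applies depends on which test carries efficacy, and the plan leaves that open.

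The documents do not support saying that the analysis will be run without accounting for patient, that the efficacy claim is necessarily inflated, or that planning figures for the next trial would be wrong.

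**What to change.** In Statistical analysis and in the Abstract, replace the ANOVA sentence with a repeated-measures analysis that includes patient. Either of these would do:

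- a mixed (split-plot) ANOVA with patient nested in treatment; or
- a linear mixed model with treatment, visit and treatment-by-visit as fixed effects, patient as the repeated unit, and small-sample degrees of freedom such as Kenward-Roger.

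If a repeated-measures ANOVA was intended all along, saying so is enough for the error term.

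State also where efficacy is read: from the treatment-by-visit contrasts, or from the post-operative visits with baseline as a covariate. A treatment main effect that includes baseline should not be used even with a patient term, because it averages in a pre-treatment visit. A 1-SD effect at three of four visits becomes (0 + 1 + 1 + 1)/4 = 0.75 SD.

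The cost is a sentence or two of wording, with no new patients or measurements. The downside is that the treatment main-effect test becomes less favourable, since it is judged on 18 degrees of freedom with the between-patient error. The treatment-by-time test becomes more sensitive.

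### The two-way ANOVA names no baseline covariate and leaves open whether baseline is a time level and which effect tests treatment; adjusting for baseline MUNE is a nearly free gain

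*Protocol article*

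**What the plan says.** The Statistical analysis section of the protocol article sets one model for all primary and secondary outcomes: "two-way ANOVA with the treatment groups and time points being the independent factors". The Methods part of the abstract repeats it: "The outcome measures will be analyzed using two-way ANOVA, with treatment assignment and time points being the independent factors". Both name two factors. Neither names a covariate, a change score or an interaction. The follow-on step is "If significant associations are detected, a post hoc analysis will be done for pairwise comparisons", without saying which effect has to be significant.

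Two sections bear on what the time points are. Secondary outcomes says "All outcome measures will be monitored at baseline, 3 months, 6 months and 12 months", which gives four. Primary outcome says "To quantify treatment response, MUNE will be repeated at 3, 6 and 12 months post-operatively", which gives three. Primary outcome also says that "MUNE will also serve as a screening tool for eligibility for the trial", so a pre-treatment value exists for every randomised patient.

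The abstract plans ten patients per group. The Sample size section says that the effect size will be judged on MUNE and will supply the sample size calculation for the full trial.

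**The concern.** Baseline MUNE is probably the best available predictor of later MUNE, and it is already measured. A two-factor model without it leaves between-patient variation in the error term that could be removed.

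The wording also allows a worse case. If baseline is one of the time levels and treatment is tested by its main effect, the arm difference is averaged over a visit at which no drug has been taken. At that visit the expected difference is zero under randomisation, and the observed difference is chance alone.

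Two things are at stake: precision in a trial of 20 patients, and the meaning of the MUNE effect size handed to the next trial.

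**Working it through.** **Inputs from the article.** 10 per arm, 20 in total (2 × 10 = 20). Visits at baseline, 3, 6 and 12 months. Two factors, no covariate.

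**Assumed inputs.** The article gives no alpha, effect, SD or correlation, so it has no power figure to reproduce. I assume two-sided 0.05, SD 1 at each visit, the same within-patient correlation ρ between any two visits, no dropout, patients treated as the repeated unit, and a true effect δ = 1 SD that is constant over the three post-operative visits.

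**What each reading estimates**
- Four-level time, treatment main effect: (0 + δ + δ + δ)/4 = 0.75δ.
- Three-level time, treatment main effect: (δ + δ + δ)/3 = δ, with baseline unused.
- Four-level time, interaction: a 3-df test of whether the arm difference changes across visits. Baseline acts as the reference.
- Post-operative mean adjusted for baseline (ANCOVA): δ.

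**Variance per patient**
- Four-visit mean: (1 + 3ρ)/4, which is 0.625 at ρ = 0.5 and 0.775 at ρ = 0.7.
- Three-visit mean: (1 + 2ρ)/3, which is 0.667 and 0.800.
- Three-visit mean adjusted for baseline: (1 + 2ρ)/3 − ρ², which is 0.417 and 0.310.

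The standard error of an arm difference is √(2 × variance/10). At ρ = 0.7 the four-visit mean gives √(2 × 0.775/10) = 0.39 around an estimate of 0.75. The adjusted mean gives √(2 × 0.310/10) = 0.25, or about 0.26 once the baseline slope is estimated, around 1.00.

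**Power with 10 per arm and a constant 1 SD effect.** The main effects come from the noncentral t with 18 df. The interaction and ANCOVA come from 60,000 simulated trials per setting, which also reproduced the main-effect figures.

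| Test | ρ = 0.3 | ρ = 0.5 | ρ = 0.7 |
|---|---|---|---|
| Main effect, four visits | 63% | 52% | 44% |
| Main effect, three visits | 82% | 74% | 66% |
| Interaction, four visits | 44% | 59% | 83% |
| Baseline-adjusted post-operative mean | 87% | 88% | 96% |

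**Sample size relative to ANCOVA** (approximate, ignoring estimation of the slope)
- Three-visit main effect: 0.667/0.417 = 1.6 at ρ = 0.5 and 0.800/0.310 = 2.6 at ρ = 0.7.
- Four-visit main effect: (0.625/0.75²)/0.417 = 2.7 and (0.775/0.75²)/0.310 = 4.4.

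**Effect that builds up** (0.33, 0.67 and 1.0 SD at 3, 6 and 12 months, ρ = 0.7). The interaction and the adjusted post-operative mean are equal at about 69%. The four-visit main effect has 23%.

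**Chance imbalance.** The baseline arm difference has SD √(2/10) = 0.45 SD, so a gap above 0.5 SD arises in about 26% of trials of this size. Adjustment allows for such a gap. A main effect does not.

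**Planning consequence.** If the four-visit main effect were carried forward with an otherwise correct SD, the next sample size would be inflated by 1/0.75² = 1.78.

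**The case against.** The strongest reply is that the worst case is not in the text. A reader might infer that the ANOVA does use baseline as a time level. The Secondary outcomes section makes that plausible, but no sentence says it, and Primary outcome ties treatment response to "MUNE will be repeated at 3, 6 and 12 months post-operatively". A reader might also infer that the treatment main effect is the headline test. The article does not say so. When baseline is a level, the interaction is the usual treatment test, and baseline is then neither averaged in nor wasted. This stands: the 25% dilution is conditional on both inferences.

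It is also tempting to set the 23% of the four-visit main effect under a building-up effect against the 82% of a baseline-adjusted 12-month comparison. That is not like for like, because it pits an average against the single visit where the effect was assumed largest. The adjusted post-operative mean, which is the fair comparator, has about 69%, the same as the interaction. ANCOVA therefore does not win in every setting.

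Nor does the article say that change within an arm will be read as a drug effect, or that the planning effect size will be the ANOVA main effect. It plans to compare the arms on demographics ("Demographic data will be compiled and analyzed for differences"); testing those differences is a separate reporting matter.

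The article calls the study exploratory and likely underpowered (Limitations), which limits the weight of any power loss. Selecting patients more than 2 SD below the age mean may also weaken the correlation between baseline and follow-up, and with it the gain: at ρ = 0.3 the three-visit main effect has 82% against 87% adjusted.

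Finally, covariates are often left to an analysis plan. Here, however, the article does commit to a model by naming its factors, so proposing a better one is fair comment on what is written.

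**Conclusion.** The point holds in a limited form. The stated model has no baseline covariate although baseline MUNE exists for every patient, and the text fixes neither the levels of time nor the effect that tests treatment.

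For a constant effect, the baseline-adjusted comparison has more power than each of the three readings at the correlations tabulated. The gain ranges from small (three-visit main effect at ρ = 0.3) to large (four-visit main effect at ρ = 0.7). For an effect that builds up, its advantage over the interaction can vanish. The reduction to 75% applies only if baseline is a level and the main effect is the test, and the article does not establish either.

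All power figures rest on the assumed effect, correlation and alpha. This is a nearly free improvement with a needed clarification, not an error that must be fixed before the trial can be analysed.

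**What to change.** In the Statistical analysis section and the abstract, replace the two-way ANOVA by a repeated-measures model of the 3-, 6- and 12-month values, with treatment, visit and their interaction, the patient as the repeated unit, and the matching baseline value of each outcome as a covariate. State that baseline is not a level of time.

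Name the treatment contrast in advance, for example the arm difference averaged over the three visits or the difference at 12 months. Report it for MUNE as a baseline-adjusted between-arm difference with its 95% CI, and say in the Sample size section that this is the effect size carried into the full-trial calculation, together with the SD that belongs to the same contrast.

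The cost is one degree of freedom for the covariate and a change of wording. No visit, measurement or patient is added.
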